### Intervention

#### Test group (massage with probiotic group)

The acupuncture points and areas are as follows: Zhongwan (RN12), Tianshu (ST25), Guanyuan (RN4), Qi Hai (RN6), Pishu (BL20), Shenshu (BL23), Dachangshu (BL25), Mingmen (DU4), Zusanli (ST36), Zhi Gou (SJ36) and abdomen. The locations of all selected acupoints are shown in Table 1. Operations: (1) Using the one-finger meditation massage method, the patient is in a supine position, and the operator uses the one-finger meditation massage method to push ST25, RN4, RN6, and RN12 for 2 min each; the one-finger meditation massage method requires concentration, sinking shoulder, dropping elbow, hanging wrist, palm deficiency, finger solid, tight pushing, and slow moving. The frequency of swinging is approximately 120–160 times/min; (2) Two minutes of clockwise abdominal massage; (3) Press and knead SJ36 and ST36 points for 1 min each; (4) The patient is in a prone position and rubs the lumbar back, BL23, DU4, BL20, and BL25 for approximately 2 min to penetrate the heat. The manipulation should be even, gentle, persistent, and powerful to achieve deep penetration; (5) Course of treatment: 10 days once, 3 times as a course of treatment, three consecutive courses of treatment (i.e., three months). The patient were given Bifidobacterium trifolium capsules (Shanghai Xinyi Pharmaceutical Co., Ltd., State Drug Administration S0950032) 630 mg/d, 3 times/d, 30 min after the meal for three months.

**Table 1 Tab1:** Location of acupoints for treating IBS-C

Acupoints	Location
Zhongwan(RN12)	On the anterior median line, midpoint of the line connecting the lower end of the sternum and the belly button
Mingmen(DU4)	Interspinous process of the second and third lumbar vertebrae
Guanyuan(RN4)	In the lower abdomen, on the anterior median line, when the umbilicus is 3 cun below the middle.
QiHai(RN6)	In the lower abdomen. On the front median line, 1.5 cun below the middle of the umbilicus
Pishu(BL20, bilateral)	Under the spinous process of the 11th thoracic vertebra, open 1.5 cun laterally
Shenshu(BL23, bilateral)	Under the spinous process of the 2th lumbar vertebra, open 1.5 cun laterally
Dachangshu(BL25, bilateral)	Under the spinous process of the 4th lumbar vertebra, open 1.5 cun laterally
Tianshu(ST, bilateral)	In the abdomen, at the same level as the navel, 2 cun away from the front median line.
Zusanli(ST36, bilateral)	Three cun below Dubi (ST35), one finger -breadth (middle finger) from the anterior crest of tibia
ZhiGou(SJ36, bilateral)	On the dorsal side of the forearm, on the line between Yangchi and the tip of the elbow, 3 cun above the transverse wrist line, between the ulna and the radius

### Control group (probiotic group)

The patients were given Bifidobacterium trifolium capsules (Shanghai Xinyi Pharmaceutical Co., Ltd., State Drug Administration S0950032) 630 mg/d, 3 times/d, 30 min after the meal; the course of treatment were three months. Patients were advised to cultivate good lifestyle habits, avoid dairy products, soybeans, and other gas-producing foods and encouraged to consume moderate amounts of high-fiber foods.

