**Methods/design:**

This is a randomized controlled trial. Eligible patients with irritable bowel syndrome (IBS-C) wererandomized 1:1 to a test group (massage plus probiotics) and a control group (probiotics). Patients in the test group weretreated once every 10 days for three consecutive courses of treatment (i.e., three months) and weregiven Bifidobacterium trifolium capsules 630 mg/dose three times daily 30 min after meals every day during the treatment period, with follow-up observations at the end of the third and sixth months of the treatment period. The control group weregiven Bifidobacterium trifolium capsules 630 mg/dose, 3 times a day for 3 months, with follow-up observations at the end of the third and sixth months of the treatment period. The primary outcome indicators are the concentrations of 5-HT and substance P and the IBS Severity Scale (IBS-SSS) assessment. Secondary outcomes are the Bristol Rating Scale (BRSA) score, the IBS Quality of Life Questionnaire (IBS-QOL scale) score, and the assessment of the effectiveness of the evidence. The results wereassessed at the pretreatment, posttreatment, and follow-up stages. Any side effects weresubject to assessment.

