### Randomization and allocation concealment

An independent statistician who is not involved in the study will generate the randomization group: the numbers were randomly divided into two Groups A and B at a ratio of 1:1, i.e., A (Test group: Massage with the probiotic group) and B (Control group: probiotic group), using SPSS 19.0 software before the formal trial. The random sequence of the generated numbers and the grouping information were kept by the person in charge and kept confidential. Opaque brown envelopes were made according to the number of included cases, and the envelopes were numbered sequentially according to the order of numbers on the surface of the envelopes. The envelopes will contain the grouping information corresponding to the random sequence of numbers on the surface of the envelopes, such as 1(A) and 2(B). After signing the informed consent form and completing the basic information form, the envelopes were opened strictly in the order of the numbers on the envelopes, and patients were allocated to groups (trial or control) in accordance with the protocol in the envelopes.

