##### IBS Severity Scale (IBS-SSS) assessment

Outcomes included the level of abdominal pain, frequency of abdominal pain, level of bloating, bowel satisfaction and effects on life. (1) Abdominal pain severity, frequency of pain in the abdomen, abdominal distension degree, defecation satisfaction, and effects on life were included. (2) Abdominal pain frequency score: abdominal pain frequency score = actual abdominal pain days/14 × 100. (3) IBS-SSS scale total score: IBS-SSS scale total score = abdominal pain severity score + abdominal pain frequency score. IBS-SSS scale total score = abdominal pain score + abdominal pain frequency score + abdominal distension score + bowel satisfaction score + impact on life satisfaction score + impact on life score.

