#### Statistical methods

##### Sample size

The test group sample size (massage with the probiotics group) and the control group (probiotics group) were randomly grouped in a 1:1 ratio, and the sample size was determined according to the bilateral hypothesis test, setting the test criterion as a = 0.05 (bilateral) and test efficacy as β = 0.20. The efficiency of the test group in the preexperimental observation is 90, and the efficiency of the control group is 60. The required sample was calculated to be approximately 60 cases, with an increase of 10% of cases taken off, and the actual sample size is approximately 66 cases; that is, 33 cases in the test group and 33 cases in the control group are selected.

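### Diet and lifestyle advice is written under the control arm only; followed as written, it is an unequal co-intervention and the between-arm difference does not isolate massage

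*Protocol article*

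**What the plan says.** The protocol article describes the two arms in separate sections.

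- **Control group (probiotic group).** After the probiotic regimen comes this advice: "Patients were advised to cultivate good lifestyle habits, avoid dairy products, soybeans, and other gas-producing foods". Patients were also "encouraged to consume moderate amounts of high-fiber foods".
- **Test group (massage with probiotic group).** This section sets out the acupoints, the manipulation and the course of treatment, then repeats the probiotic (product, manufacturer, approval number, dose) and ends at "630 mg/d, 3 times/d, 30 min after the meal for three months". It contains no diet or lifestyle advice.

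The intended contrast is stated elsewhere without any advice. The abstract describes randomization "1:1 to a test group (massage plus probiotics) and a control group (probiotics". The section on randomization and allocation concealment labels the groups "A (Test group: Massage with the probiotic group) and B (Control group: probiotic group".

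**The concern.** In an add-on design, everything except the added treatment should be the same in both arms. Here a second element, the advice, is recorded for one arm only. Randomization does not protect against this, because the difference arises after allocation. The planned independent-sample and chi-square tests cannot separate the two components either.

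The advice bears on what the trial measures. The Background section itself says that IBS is diet-related in about two-thirds of people. The IBS-SSS, a primary outcome, includes "level of bloating, bowel satisfaction and effects on life" alongside two pain items, and advice on gas-producing foods and fiber could move the bloating and bowel-satisfaction components. Stool form on the Bristol scale, a secondary outcome, is exposed in the same way.

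The Objective section aims to show better long-term efficacy than drug treatment alone. A control arm that also receives dietary advice is not drug treatment alone.

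**Working it through.** **1. The text side by side**

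| Element | Test group section | Control group section |
|---|---|---|
| Massage | yes | no |
| Probiotic | yes, restated in full | yes, stated in full |
| Lifestyle habits; avoiding dairy, soybeans and gas-producing foods | not mentioned | yes |
| Moderate high-fiber foods | not mentioned | yes |

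The shared drug is written out in both sections, so a reader cannot assume that something named in one arm applies to both. No other section extends the advice to the test arm.

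**2. The plan's own sample size**

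Inputs from the Sample size section: "The efficiency of the test group in the preexperimental observation is 90, and the efficiency of the control group is 60" (read as percentages), two-sided alpha 0.05, beta 0.20, allocation 1:1.

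- Arcsine formula: h = 2·asin(√0.90) − 2·asin(√0.60) = 0.726. Then n = 2(1.960 + 0.842)²/h² = 2 × 7.849/0.527 = 29.8, so 30 per arm and 60 in total.
- Adding 10% for dropout: 60 × 1.10 = 66, or 33 per arm.

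The stated figures reproduce. The illustrations below use 30 per arm, the number required before the dropout allowance.

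**3. Illustration on the efficacy rate**

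The document gives no effect of the advice, so the shifts here are assumptions. The efficacy rate is the quantity used to size the trial; graded efficacy itself is a secondary outcome.

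With x and y responders out of 30 per arm and s = x + y, the uncorrected statistic is χ² = 60(x − y)²/[s(60 − s)]. Power is the sum of Bin(x; 30, 0.90) × Bin(y; 30, control rate) over all pairs with χ² > 3.84.

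| Control rate | Power |
|---|---|
| 50% | 0.949 |
| 55% | 0.891 |
| 60% (planned) | 0.796 |
| 65% | 0.661 |
| 70% | 0.499 |

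If the pre-experimental 60% was already observed under the advice, planned power stays at 0.80. The contrast is still not massage alone.

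**4. Illustration on the IBS-SSS**

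No SD is given, so the scale is SD units. For a two-sample t-test (noncentral t, 58 df, 30 per arm, two-sided alpha 0.05), the difference detectable with 80% power is 0.736 SD. Suppose the true massage effect equals that value and the advice shifts the control arm:

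| Assumed shift from advice | Share of detectable difference | Power if gap narrows | Power if gap widens |
|---|---|---|---|
| 0.1 SD | 0.1/0.736 = 14% | 0.678 | 0.889 |
| 0.2 SD | 0.2/0.736 = 27% | 0.532 | 0.946 |

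**The case against.** The strongest reply is that the sentence is misplaced. It closes the whole description of the interventions, its subject is patients in general, and every definition of the comparator names the probiotic or pharmacotherapy only. That fits background care written once at the end, and a condensed article may leave such detail to the full protocol. This reading is plausible. But the difficulty is where stated text is placed, not missing detail: the sentence sits under the control heading, and a reader who follows the document would give the arms different care.

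A second reply is that advice is given to help, so control-only advice would work against massage and a positive result would be conservative. This is reasonable as an expectation, but the document does not establish it; fiber or food avoidance might worsen bloating or pain in some patients. Dilution would also do harm, because a null result could not be read as absence of a massage effect.

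Third, every shift in the power tables is assumed, and planned power is unaffected if the 60% already includes the advice. Both points stand, which is why the figures are only illustrations. It also stands that no route to serum 5-HT or substance P, the other primary outcomes, has been shown.

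Finally, equal advice would not match the therapist contact that only the test arm receives. That is true, but it is a separate difference and does not justify this one.

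**Conclusion.** The concern holds. As written, the arms differ by massage and by diet and lifestyle advice, and a between-arm difference could not be attributed to massage alone. The outcomes most plainly exposed are the bloating and bowel-satisfaction components of the IBS-SSS (2 of 5) and stool form.

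The direction and size of any bias cannot be determined from the document. Under the assumed shifts, a movement of 5 points in the control rate changes power from 0.80 to 0.66 or 0.89, and a 0.1 SD shift on the IBS-SSS is 14% of the detectable difference.

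Confidence is medium, because a drafting slip could account for the placement. The point should be corrected, and the sample size need not change.

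**What to change.** Give identical written diet and lifestyle advice to both arms, or to neither, and state it once before the two arm descriptions as common background care. The content of the advice is for the investigators to decide.

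- If both arms did receive the advice, move the sentence out of the control section and say so.
- If patients have already been treated under the unequal version, say so and describe the contrast as massage plus probiotic versus probiotic plus dietary advice.

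The cost is one relocated sentence and the same written advice for both arms, with no additional patients. If treatment has already been unequal, rewording makes the description accurate but cannot recover the massage-only contrast for those patients.

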### Outcome measures

#### Primary outcome

##### 5-HT and SP concentration

Serum 5-HT and SP concentrations in patients were determined before and after treatment using an enzyme-linked immunosorbent assay (ELISA). The level of 5-HT is closely related to the presence of diarrhea or constipation in irritable bowel syndrome, as well as SP [55, 56]. We will compare the efficacy of the two groups by ELISA of serum 5-HT and SP in patients before and after treatment.

##### IBS Severity Scale (IBS-SSS) assessment

Outcomes included the level of abdominal pain, frequency of abdominal pain, level of bloating, bowel satisfaction and effects on life. (1) Abdominal pain severity, frequency of pain in the abdomen, abdominal distension degree, defecation satisfaction, and effects on life were included. (2) Abdominal pain frequency score: abdominal pain frequency score = actual abdominal pain days/14 × 100. (3) IBS-SSS scale total score: IBS-SSS scale total score = abdominal pain severity score + abdominal pain frequency score. IBS-SSS scale total score = abdominal pain score + abdominal pain frequency score + abdominal distension score + bowel satisfaction score + impact on life satisfaction score + impact on life score.

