##### IBS Quality of Life Questionnaire (IBS-QOL scale)

The total score of the scale and the score of each dimension of the scale were calculated separately. The scale consists of 8 dimensions: poor mood, behavioral disorders, self-image, health concerns, avoidance of food, social functioning, sexual behavior and expansion of relationships. The total scale score and each dimension score were converted into standard scores according to the following formula. Standard score = (actual score sum of each item - theoretical minimum score/theoretical score range) ×100%.

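### The IBS-SSS total, a primary outcome, is given by two incompatible equations, and neither equals the sum of the five listed components

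*Protocol article*

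**What the plan says.** The abstract (Methods/design) states: "The primary outcome indicators are the concentrations of 5-HT and substance P and the IBS Severity Scale (IBS-SSS) assessment". The section on the IBS-SSS assessment, under Primary outcome, names the components twice. Its opening sentence reads "Outcomes included the level of abdominal pain, frequency of abdominal pain, level of bloating, bowel satisfaction and effects on life", and its item (1) reads "Abdominal pain severity, frequency of pain in the abdomen, abdominal distension degree, defecation satisfaction, and effects on life were included". The two lists agree in content and order, and each has five entries.

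Item (2) scales one component: "abdominal pain frequency score = actual abdominal pain days/14 × 100". Item (3) then defines the total in two successive equations:

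- The two-term equation: "IBS-SSS scale total score = abdominal pain severity score + abdominal pain frequency score".
- The six-term equation, which begins "IBS-SSS scale total score = abdominal pain score + abdominal pain frequency score + abdominal distension score" and goes on to add bowel satisfaction, an "impact on life satisfaction score" and a separate life-impact score.

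Under Secondary outcome, the IBS-QOL section converts the total and each dimension to a standard score. Its bracket encloses the item sum minus "theoretical minimum score/theoretical score range", closes after the range, and the result is multiplied by 100%.

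**The concern.** Both equations in item (3) carry the same label, yet they cannot both define one quantity. Neither matches the component list given just above them.

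The choice changes what is measured. The abstract names constipation, abdominal pain and abdominal distension as the main manifestations of IBS-C, and the Background says the trial looks for benefit beyond bowel motility. The two-term total contains neither distension nor bowel satisfaction, so a patient who improved only on those would show no change. The six-term total needs a score that the document does not describe. A published definition that leaves the total open also leaves room to settle it after the data are seen.

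The IBS-QOL bracket raises a smaller matter of the same kind. Followed literally, it does not give a score from 0 to 100%.

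**Working it through.** There is no figure in the plan to reproduce here, so the check is a count of terms followed by an illustration.

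**1. Terms in each definition (from the IBS-SSS section)**

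| Component | Listed | Two-term equation | Six-term equation |
|---|---|---|---|
| Pain severity | yes | yes | yes |
| Pain frequency | yes | yes | yes |
| Distension | yes | no | yes |
| Bowel satisfaction | yes | no | yes |
| Impact on life satisfaction | no | no | yes |
| Effect on life | yes | no | yes |
| Count | 5 | 2 | 6 |

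This step uses no assumption.

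**2. Range of the total.** Pain frequency is days/14 × 100, so 0, 7 and 14 days give 0, 50 and 100. The document gives no range for the other components. Assume 0 to 100 for each:

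- Two terms: 2 × 100 = 200.
- Five listed components: 5 × 100 = 500.
- Six terms: 6 × 100 = 600.

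**3. Effect on a measured change.** Take a patient with 50 on every term. The baseline totals are 100 (two terms), 250 (five) and 300 (six). Let both pain terms halve, a fall of 25 + 25 = 50 points:

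- Two terms: 100 to 50, and 50/100 = 50%.
- Five components: 250 to 200, and 50/250 = 20%.
- Six terms: 300 to 250, and 50/300 = 17%.

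If distension and bowel satisfaction halve instead, the two-term total stays at 100 (0%), while the other two again fall by 20% and 17%. The totals are therefore not rescalings of one another, and a between-group comparison can differ according to which is used.

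**4. IBS-QOL.** Let S be the item sum, m the theoretical minimum and R the theoretical range.

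- As printed: (S − m/R) × 100%.
- With the subtraction bracketed: [(S − m)/R] × 100%.

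The document gives neither the number of items nor their scoring. Under assumed values:

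| Assumed items and scoring | m | R | Printed, lowest to highest | Rebracketed |
|---|---|---|---|---|
| 10 items, 1 to 5 | 10 | 40 | 975% to 4975% | 0% to 100% |
| 34 items, 1 to 5 | 34 | 136 | 3375% to 16975% | 0% to 100% |
| 34 items, 0 to 4 | 0 | 136 | 0% to 13600% | 0% to 100% |

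For example, 10 items scored 1 to 5 with S = 30 give (30 − 10/40) × 100 = 2975% as printed, and (30 − 10)/40 × 100 = 50% rebracketed.

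Both forms are increasing straight-line functions of S: the slope is 100 in one and 100/R in the other, and both subtract 100 × m/R. A t-test on either would give the same p-value. The fault therefore affects the reported scale and the comparability of dimensions with different R, but not the test itself.

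**The case against.** The best case for the document is that the intended total can be recovered. The five components appear twice in the same order, and the six-term equation follows that order. The two-term equation looks like a truncated start of the longer one. The unlisted term looks like a merging of its neighbours, bowel satisfaction and impact on life. On this view it is a drafting or translation fault, not a pair of rival endpoints. As a reading of the origin, that is probably right. It does not settle the matter, because a reader must discard one printed equation and edit the other to reach a sum that the article never states. Nor is this detail left to a fuller document: the article chose to state the rule and stated it two ways.

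Several further objections stand and limit the point:

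- **Double counting.** A reader might infer that the six-term total counts life impact twice, giving it 2/6 = 33% of the weight. That is only one reading of the unlisted term, and it needs equal component ranges as well. The document does not say what the term measures or that a sixth item is collected.
- **A 0 to 500 scale.** A reader might take this as the documented range. Only pain frequency is scaled to 100 in the text, so the other four ranges need confirming.
- **Bias.** Any one equation would apply to both arms. The ambiguity changes what is measured but does not of itself favour an arm.
- **Sample size.** The calculation uses efficiencies of 90 and 60, not IBS-SSS or IBS-QOL scores, so it is unaffected.
- **IBS-QOL.** A reader might infer that nonsensical scores will be reported. The reference to standard scores, a minimum, a range and a percentage leaves one sensible reading, and the outcome is secondary. That the article does not give the direction of scoring is ordinary condensation and is not part of this point.

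**Conclusion.** The point holds. As printed, a primary outcome has two incompatible definitions of its total, with two and six terms, and neither equals the five components listed twice in the same section. No other part of the article resolves it. This rests on the text alone.

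The size is illustrative. If each component runs 0 to 100, the maximum total is 200 or 600 under the printed equations, against 500 for the listed components. The same fall in pain would read as 50%, 17% or 20% respectively for a patient who starts at 50 throughout.

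The IBS-QOL bracket is wrong as written but minor. Its intended form is plain and the outcome is secondary.

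The document does not show that life impact is counted twice, that a sixth item is collected, or that the comparison is biased.

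**What to change.** In the IBS-SSS section, keep one definition: total = pain severity + pain frequency (days/14 × 100) + distension + bowel satisfaction + effect on life. Delete the two-term equation and the unlisted term. The sponsor should confirm the range of each component and state the range of the total that follows from it.

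In the IBS-QOL section, write the standard score as [(sum of item scores − theoretical minimum) / theoretical score range] × 100%.

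The cost is two corrected formulas and a statement of the component ranges. No new data are needed.
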